**Figure 1 fig1:**
[figure not shown]
Gantt chart outlining the 24-month project timeline and task allocation. Key activities include: administrative and ethics clearance; research training; retrospective data collection; definition of prognostic parameters and data-management protocols; software system design; development and validation of manual and semi-automated MRI segmentation tools; implementation of Machine Learning and Deep Learning classification frameworks; statistical integration of methods; overall analysis, manuscript drafting, and result dissemination; and recurring project meetings. Colour coding denotes responsibility: grey bars indicate tasks conducted by all partners, orange bars those led by the computer science centres, and blue bars those led by the medical centres.

From month 7 through month 24, the focus shifts to development, integration and validation of the prototype ML- and DL-based predictive prognostic models. Retrospective data will be used to train separate ML and DL models aimed at predicting the spread of GB recurrence. These models will be refined iteratively and integrated into a unified framework of prototype ML- and DL-based predictive prognostic models, which will then be applied to prospective data as it becomes available.

Concurrently, an automated segmentation software prototype will be deployed and optimized throughout this period. All software components, from preprocessing pipelines to the predictive prognostic models and segmentation modules, will undergo continuous testing and improvement.

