### Study population and sample size

We will retrospectively identify all consecutive patients with histologically confirmed aggressive high grade glioma who experienced a recurrence and underwent treatment between January 2014 and December 2020.

This time frame was selected to ensure an adequate follow-up duration for most patients, allowing for meaningful analysis of recurrence patterns and survival outcomes. Based on institutional records, approximately 200 patients are expected to meet the initial screening criteria.

Enrollment will be based on the following inclusion criteria (Figure 2):

Histopathological diagnosis of glioblastoma or diffuse astrocytoma, reclassified according to the 2021 WHO CNS tumor classification:

i IDH-wildtype glioblastoma (CNS WHO grade 4), orii IDH-mutant astrocytoma, grade 4.

Availability of molecular markers (IDH mutation status, MGMT promoter methylation, etc.), when tested.Radiologically or histologically confirmed recurrence.Sufficient clinical and radiological follow-up, defined as a minimum of 24 months or until documented disease progression or death.

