**Figure 2 fig2:**
[figure not shown]
Study flowchart showing patient selection, inclusion/exclusion criteria, and outcome analysis. IDH, isocitrate dehydrogenase; MGMT, O6-methylguanine-DNA methyltransferase; PFS, progression-free survival; OS, overall survival.

By including cases up to December 2020, we ensure a follow-up window extending at least to 2024–2025, which is crucial given the potential for long survival in patients with IDH-mutant tumors.

Needle biopsies, second surgeries, and patients lost to follow-up will be excluded. Calculating an approximate 30% dropout rate due to the exclusion criteria, we would enroll around 140 patients in the final analysis.

While traditional power calculations and formal sample size justifications are challenging for exploratory high-dimensional radiomic studies, a final cohort of approximately 140 patients is considered methodologically adequate for classical Machine Learning applications. To mitigate the risk of overfitting and directly address the potential class imbalance between local and distant recurrences, we will implement data augmentation and synthetic resampling techniques (such as the Synthetic Minority Over-sampling Technique, SMOTE) on the extracted radiomic features, ensuring robust and generalizable model training.

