### Outcome

#### Primary outcome

Prototype ML- and DL-based predictive prognostic models capable of forecasting the *spread of recurrence*, intended as the predicted site of recurrence relative to the original surgical cavity. In this context, *spread* refers to the spatial distribution of tumor cell regrowth—whether it occurs locally (within 2 cm or on residual tissue) or extends toward more distant brain regions. The first class is Local/Residual recurrence, defined as tumor regrowth strictly within 2 cm of the resection cavity or progressing from residual tumor tissue. The second class is Distant spread, defined as the emergence of tumor cells extending toward more distant brain regions beyond the 2 cm margin, including mixed patterns where both local and distant recurrences are simultaneously present.

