After the contouring and segmentation steps, a set of feature descriptors will be extracted from the segmented volumes of interest to enable supervised pattern recognition using ML techniques. Initially, expert radiologists will manually perform the segmentation process. However, as the study progresses, we will also develop a semiautomatic segmentation tool designed to support and streamline the radiologists’ workflow.

In the ML-based analysis, the extracted features will include a combination of specific clinical variables (as detailed in the “Data Collection” and “Radiological Parameters” sections), semantic descriptors derived from diagnostic imaging, and agnostic radiomic features that are independent of anatomical context (13).

Once the clinical and imaging feature vectors are defined, the resulting dataset will contain a large number of variables relative to the number of cases available. This imbalance may lead to what is commonly referred to as the “curse of dimensionality,” a situation in which the high dimensionality of the data reduces classification performance. This occurs because the number of samples required to accurately estimate complex relationships grows exponentially with the number of features.

To mitigate this issue, a dimensionality reduction step will be incorporated. This step will eliminate redundant or irrelevant features and retain only the most informative variables, thereby enhancing both model performance and computational efficiency (14). We will employ feature extraction techniques such as Principal Component Analysis (PCA), Independent Component Analysis (ICA), and Fisher Linear Discriminant Analysis (FLDA), which generate new, reduced-dimensional feature sets from the original data. In parallel, we will apply feature selection methods aimed at identifying a subset of the most predictive features while discarding those that do not contribute meaningfully to classification accuracy.

An added benefit of feature selection lies in improving the interpretability of ML models. By isolating the most relevant features, the process supports human-understandable insights into the decision-making process and helps reduce the so-called “black box” nature often associated with ML algorithms, thus contributing to model explainability (15).

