Classification of the extracted feature vectors will be carried out using conventional feed-forward Artificial Neural Networks, Support Vector Machines (SVM), Decision trees, Multi layer perceptron (MLP) (10, 11, 16–18) and other established classification algorithms (19). To enhance predictive performance, ensemble learning methods such as Random Forests will also be explored.

To ensure a robust evaluation and mitigate the risk of optimistic performance estimates, model validation will be conducted using a nested repeated stratified k-fold cross-validation framework. This rigorous approach prevents data leakage by explicitly separating hyperparameter optimization, which is executed using grid search or randomized search within the inner cross-validation loop, from the final unbiased performance assessment conducted on the hold-out folds in the outer loop. Crucially, to preserve the strict separation between training and testing cohorts, all data transformation procedures, including dimensionality reduction, feature selection, and the application of data augmentation techniques such as SMOTE, will be fitted exclusively on the training folds and subsequently applied to the corresponding independent validation folds. Model performance will be assessed using Receiver Operating Characteristic (ROC) curves, along with sensitivity and specificity metrics (Figure 4).

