**Figure 4 fig4:**
[figure not shown]
Machine learning pipeline. Workflow diagram of the proposed Radiomics pipeline for Glioblastoma recurrence and location prediction. Preoperative MRI scans are first processed as input images, then undergo segmentation to delineate tumor volumes. Next, quantitative feature calculation extracts agnostic (texture, shape) and semantic (clinical) descriptors. The resulting high-dimensional feature set is trimmed via dimensionality reduction (feature selection and extraction), and a Classification model construction step trains a predictive algorithm. Finally, the Decision Support System: prediction of recurrence and its location integrates the model output to inform clinical follow-up and treatment planning.

Given the sample size boundaries, classical Machine Learning algorithms will serve as the primary and most clinically interpretable analytical framework for the prediction of recurrence spread. The classification capabilities of DL, specifically pre-trained convolutional neural networks (CNNs) such as AlexNet, SqueezeNet, ResNet, and GoogLeNet (Figure 5) (20), will be assessed as an exploratory secondary analysis to evaluate potential performance gains over classical ML These networks will be fine-tuned using different training strategies, including three configurations involving partial weight freezing, as well as training from scratch. Additionally, the CNNs will be used as feature extractors, whereby the learned feature representations are passed to classical ML classifiers, for example SVMs. This hybrid approach leverages the representational power of CNNs while benefiting from the simplicity and efficiency of some ML algorithms, which are particularly suitable for high-dimensional classification tasks such as those involved in this study.

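### The outer loop is unbiased for each fixed pipeline, but the plan does not secure this for a model chosen among 20 to 40 competing pipelines

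*Protocol article*

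**What the plan says.** **Validation.** The Analysis section specifies nested repeated stratified k-fold cross-validation. Grid or randomized hyperparameter search runs in the inner loop. The outer loop is described as "the final unbiased performance assessment conducted on the hold-out folds in the outer loop". Reduction, feature selection and SMOTE are fitted on the training folds and then applied to the held-out folds.

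**Candidates.** The same section names feed-forward neural networks, SVM, decision trees, multilayer perceptrons, Random Forests and further unnamed algorithms. On reduction it says "We will employ feature extraction techniques such as Principal Component Analysis (PCA), Independent Component Analysis (ICA), and Fisher Linear Discriminant Analysis (FLDA"), with feature selection in parallel; the Abstract names LASSO. Four CNN architectures follow, with "three configurations involving partial weight freezing, as well as training from scratch", and CNN features are also passed to classical classifiers.

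**Development.** The Study design section says of the models trained on the retrospective data: "These models will be refined iteratively and integrated into a unified framework".

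**Hierarchy.** The Primary outcome section reads "Prototype ML- and DL-based predictive prognostic models capable of forecasting the" spread of recurrence, which places ML and DL side by side. The Analysis section makes classical ML the primary framework and CNN classification an exploratory secondary analysis.

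**Size.** Under Study population and sample size, "approximately 200 patients are expected to meet the initial screening criteria", and then "Calculating an approximate 30% dropout rate due to the exclusion criteria, we would enroll around 140 patients in the final analysis". The share of distant recurrences is not given; the text refers only to "the potential class imbalance between local and distant recurrences".

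**The concern.** Nested cross-validation protects only the decisions made inside the inner loop. As described, the inner loop decides hyperparameters within a given pipeline. Which classifier and which reduction method become the reported model is a separate decision. For that decision the article describes no other development data than the outer folds of the same roughly 140 patients.

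If the winner is picked on outer-fold AUC, the reported figure is a maximum of many noisy estimates, and its expectation lies above the true AUC of the chosen model. Refining models iteratively after seeing such results adds to the same problem. With few distant recurrences each AUC is imprecise, so the excess could be material. Discrimination is the main result of this study and the basis for the planned prospective validation.

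The conflicting status of deep learning matters here because it leaves unclear how wide the set of candidates for the main result is.

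**Working it through.** **1. The plan's own figure.** 200 × (1 − 0.30) = 140. This reproduces the stated cohort. The article gives no target AUC, pipeline count or optimism figure to reproduce.

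**2. Number of pipelines.** This is a cross-product of named options, not a number in the article.
- Classical: 5 classifiers (ANN, SVM, tree, MLP, Random Forest) × 4 reductions (PCA, ICA, FLDA, LASSO) = 20.
- With two imbalance options (class weighting, resampling): 20 × 2 = 40.
- Alternatively, with the exploratory CNNs: 20 + 4 architectures × 4 training strategies + 4 CNN-feature hybrids = 20 + 16 + 4 = 40.

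**3. Precision of one AUC (Hanley–McNeil).** SE² = [A(1−A) + (n₁−1)(Q₁−A²) + (n₀−1)(Q₂−A²)] / (n₁n₀), with Q₁ = A/(2−A) and Q₂ = 2A²/(1+A). The assumed true AUC is A = 0.70, so Q₁ = 0.5385 and Q₂ = 0.5765. For an assumed distant share of 20%, n₁ = 28 and n₀ = 112:

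SE² = (0.210 + 1.308 + 9.598) / 3136 = 0.003545, so SE = 0.0595.

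For 10% (14 and 126) SE = 0.0813. For 30% (42 and 98) SE = 0.0507.

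**4. Expected excess of the best of m.** For m pipelines with equal true AUC and common correlation ρ between their estimates, excess = SE × √(1−ρ) × E[Z(m:m)]. Here E[Z(20:20)] = 1.87 and E[Z(40:40)] = 2.16.

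Example at 20% distant and ρ = 0.5: 0.0595 × 0.7071 × 1.87 = 0.079 for m = 20, and 0.0595 × 0.7071 × 2.16 = 0.091 for m = 40.

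| Distant share | m | ρ = 0.5 | ρ = 0.8 | ρ = 0.9 |
|---|---|---|---|---|
| 10% | 20 | 0.107 | 0.068 | 0.048 |
| 10% | 40 | 0.124 | 0.079 | 0.056 |
| 20% | 20 | 0.079 | 0.050 | 0.035 |
| 20% | 40 | 0.091 | 0.058 | 0.041 |
| 30% | 20 | 0.067 | 0.042 | 0.030 |
| 30% | 40 | 0.078 | 0.049 | 0.035 |

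The table runs from 0.030 to 0.124.

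**5. Check with fitted models.** Sixty synthetic datasets of 140 patients were generated per scenario. Forty untuned pipelines (5 classifiers × 4 reductions × with or without oversampling) were fitted within 5-fold training folds. The winner was taken on outer-fold AUC, and its true AUC came from 4,000 new cases.

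| Scenario | Best AUC in CV | True AUC of the chosen | Optimism (Monte Carlo SE) | Mean ρ |
|---|---|---|---|---|
| 20% distant, no signal | 0.611 | 0.500 | 0.111 (0.006) | 0.36 |
| 20% distant, signal | 0.706 | 0.615 | 0.091 (0.007) | 0.53 |
| 10% distant, signal | 0.727 | 0.580 | 0.146 (0.008) | 0.46 |
| 30% distant, signal | 0.696 | 0.620 | 0.076 (0.007) | 0.61 |

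Averaged over all pipelines in the 20% signal scenario, the cross-validated AUC was 0.598 against a true 0.601. Fitting within folds therefore works as the plan intends, and the excess comes from the selection. The 10% scenario exceeds the formula, partly because single AUCs varied more there (SD 0.102) than the SE of 0.081 used in step 3.

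**The case against.** A reader might infer that the plan will pick the best of 40 pipelines on outer-fold results and that its headline AUC is therefore inflated by 0.09. The documents do not support this.

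- **Selection is not stated.** The article does not say how the reported model is chosen, and a selection rule may stand in the full protocol or SAP. The bias is conditional.
- **Forty is the upper count.** It needs either imbalance options treated as rival candidates or CNNs that the Analysis section labels exploratory. That section ties imbalance handling to the observed class distribution, not to performance. An MLP is itself a feed-forward network, and FLDA gives one component for two classes, so even the 20 classical combinations overlap.
- **0.09 is one scenario.** It depends on an unstated class share and on assumed correlation and signal.
- **The safeguards are real.** For any fixed pipeline the described nesting separates tuning from testing.
- **The claims are tempered.** The Conclusion calls the work exploratory, the Discussion plans prospective validation, and the Study design section foresees applying the framework to prospective data.

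All of this stands, and it limits the size and certainty of the point. It does not remove it. The article states which decisions go in the inner loop and claims a property for the outer loop. With many rivals and iterative refinement, that division does not deliver the property for a selected model. Later prospective data would not correct the cross-validated AUC reported from this cohort.

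**Conclusion.** The point holds in conditional form. The outer-loop estimate is approximately unbiased for each fixed pipeline. For a model selected among the listed pipelines, the stated loop roles do not secure that.

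If selection used outer-fold AUC, the optimism would be roughly 0.03 to 0.12, and about 0.08 (20 pipelines) to 0.09 (40 pipelines) at 20% distant and correlation 0.5. This rests on 140 patients, a true AUC of 0.70 shared by all pipelines, a distant share of 10-30% and correlations of 0.5-0.9. Only the 140 comes from the article. Pipelines with clearly different true AUCs would give a smaller excess; a distant share of 10% could give a larger one, as the fitted-model check showed.

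Separately, and without any calculation, the Primary outcome and Analysis sections disagree on whether deep learning classification is primary or exploratory.

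**What to change.** - In the Analysis section, make classifier family, reduction or selection method, and any other option chosen on performance, categorical choices searched in the inner loop. The outer loop then scores the whole selection procedure once. Alternatively, pre-specify one primary classical pipeline.
- Name that single outer-loop AUC, with a patient-level 95% confidence interval, as the primary performance result. Report all other pipelines and label them exploratory.
- Reconcile the Primary outcome section with the Analysis section, so that the status of classical ML and deep learning is the same in both.

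Freezing the code before the outer loop is run and adding a clinical-only benchmark model on the same folds would be useful but are optional.

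The cost is more computing time, some rewording and possibly a lower headline AUC. The change has to be made before outer-fold results are seen, because it cannot be repaired credibly afterwards.

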**Methods and analytics:**

A multicenter retrospective collection of clinical and radiological variables will be performed for all eligible GB patients. Variables will include demographic, surgical, pathological, and preoperative MRI features. Predictive modelling will use classical ML algorithms (e.g., Random Forest, SVM, Multilayer perceptron, etc.) and a 3D U-Net architecture for DL-based image segmentation. Dimensionality reduction (PCA, LASSO, etc.) will be used to prevent overfitting and improve model generalizability. Model performance will be assessed through Area Under the Curve (AUC), P-R curve, F-score, accuracy, sensitivity, specificity, confusion matrix, and Dice score for segmentation.

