For MRI image analysis, feature extraction will be performed using the open-source PyRadiomics library, in strict compliance with the Image Biomarker Standardisation Initiative (IBSI) guidelines. To ensure standardization, all images will be resampled to an isotropic voxel size of 1x1x1 mm using B-spline interpolation prior to extraction. Image discretization will be performed using a fixed bin width approach to maintain the absolute intensity meaning of the MRI sequences. The extracted agnostic radiomic features will encompass multiple categories, including 3D shape, first-order statistics, and higher-order texture matrices such as the Gray Level Co-occurrence Matrix (GLCM), Gray Level Run Length Matrix (GLRLM), Gray Level Size Zone Matrix (GLSZM), Gray Level Dependence Matrix (GLDM), and Neighborhood Gray Tone Difference Matrix (NGTDM). To guarantee methodological robustness and address segmentation uncertainty, a reproducibility analysis will be conducted. A representative subset of cases will be independently segmented by two different expert radiologists. The Intra-class Correlation Coefficient (ICC) will be calculated for each extracted feature, and only robust features demonstrating an ICC greater than 0.75 will be retained for the dimensionality reduction and ML modeling phases. To strictly prevent any circular dependency within the study design, the radiomic feature extraction for the predictive classification models will rely exclusively on the manual segmentations performed by the expert neuroradiologists, which serve as the definitive ground truth. The development of the 3D U-Net is designated as a parallel and independent task. The automated segmentation tool will be trained on these manual annotations but will not be utilized to generate the input features for the retrospective predictive models, positioning it solely as a standalone secondary outcome for future prospective applications.

The issue of class imbalance, which may be present in the dataset, will be addressed by incorporating appropriate strategies during model training. Depending on the observed distribution, techniques such as class weighting or resampling (e.g., oversampling the minority class) may be applied to reduce potential bias and improve the model’s ability to detect less represented cases.

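### The cross-validation rule, read literally, applies SMOTE and augmentation to the validation folds, against the protocol's own aim of keeping test data separate

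*Protocol article*

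**What the plan says.** The Analysis section sets the validation design as a "nested repeated stratified k-fold cross-validation framework", with "the final unbiased performance assessment conducted on the hold-out folds in the outer loop". It then gives one rule for "all data transformation procedures, including dimensionality reduction, feature selection, and the application of data augmentation techniques such as SMOTE". All of these are to be fitted on the training folds and then carried over: "SMOTE, will be fitted exclusively on the training folds and subsequently applied to the corresponding independent validation folds". The purpose given is "to preserve the strict separation between training and testing cohorts". SMOTE is named without an exception, and nothing in the article says that validation folds contain only real patients.

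Two other places bear on the point:

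- Earlier in the Analysis section, class imbalance "will be addressed by incorporating appropriate strategies during model training". Class weighting and resampling are listed there as options that depend on the observed distribution.
- In Study population and sample size, augmentation and SMOTE are to be used "on the extracted radiomic features, ensuring robust and generalizable model training".

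The abstract lists the performance measures as "Area Under the Curve (AUC), P-R curve, F-score, accuracy, sensitivity, specificity, confusion matrix", plus the Dice score for segmentation. The Analysis section names only ROC curves, sensitivity and specificity.

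**The concern.** A principal component projection or a feature filter is learned on training data and then applied to held-out patients as a fixed mapping. SMOTE is not a mapping. It creates new minority-class records by interpolation, and held-out patients need nothing from it. Applying it to a validation fold can only add invented cases to the set being scored.

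The rule governs the evaluation of the primary outcome, the classifier of local/residual versus distant recurrence. An analyst who coded it literally could do one of two things:

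- Oversample within the validation fold, so that metrics which depend on class balance describe a prevalence that no patient group has.
- Generate validation cases with the help of training patients, so that the test set is no longer independent and discrimination looks better than it is.

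In the inner loop, the same step would distort the choice of hyperparameters.

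**Working it through.** **Inputs from the protocol article.** About 200 patients screened and 30% excluded: 200 × (1 − 0.30) = 140, which reproduces the stated cohort. The article gives no share of distant recurrence (it says only that it is rarer), no number of folds and no feature count after reduction. These are therefore assumptions below.

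**Step 1: how much of a balanced validation fold would be synthetic.** With D distant cases among 140 and 5 folds, full balancing needs (140 − 2D)/5 synthetic cases per fold. They make up (140 − 2D)/(140 − D) of the distant class.

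- 10% distant, D = 14: 112/5 = 22.4 per fold; 112/126 = 89% synthetic.
- 20% distant, D = 28: 84/5 = 16.8 per fold; 84/112 = 75% synthetic.
- 30% distant, D = 42: 56/5 = 11.2 per fold; 56/98 = 57% synthetic.

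**Step 2: effect of the artificial balance alone.** PPV = se·p / [se·p + (1 − sp)(1 − p)], and F1 = 2·PPV·se / (PPV + se). With assumed se = 0.60 and sp = 0.80:

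- p = 0.10: PPV = 0.06/(0.06 + 0.18) = 0.25; F1 = 0.30/0.85 = 0.35.
- p = 0.15: PPV = 0.09/(0.09 + 0.17) = 0.35; F1 = 0.44.
- p = 0.20: PPV = 0.12/(0.12 + 0.16) = 0.43; F1 = 0.50.
- p = 0.50: PPV = 0.30/(0.30 + 0.10) = 0.75; F1 = 0.90/1.35 = 0.67.

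Accuracy, se·p + sp·(1 − p), also moves, here downward: 0.06 + 0.72 = 0.78 at 10%, against 0.30 + 0.40 = 0.70 at 50%. The distortion is therefore not always flattering.

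**Step 3: simulation with no signal.** 140 patients, 10 pure-noise features, 5 folds, ridge logistic classifier, 5-neighbour SMOTE always applied to the training folds, 150 runs. Only the treatment of the validation fold differs.

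| Distant share | Validation fold | AUC | Average precision | F1 |
|---|---|---|---|---|
| 10% | untouched | 0.495 | 0.193 | 0.151 |
| 10% | SMOTE within fold | 0.495 | 0.510 | 0.314 |
| 10% | interpolated toward training neighbours | 0.604 | 0.581 | 0.494 |
| 20% | untouched | 0.504 | 0.287 | 0.265 |
| 20% | SMOTE within fold | 0.501 | 0.518 | 0.404 |
| 20% | interpolated toward training neighbours | 0.555 | 0.554 | 0.496 |
| 30% | untouched | 0.502 | 0.379 | 0.350 |
| 30% | SMOTE within fold | 0.501 | 0.530 | 0.441 |
| 30% | interpolated toward training neighbours | 0.527 | 0.547 | 0.484 |

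**Step 4: range over assumptions.** With 10–30% distant and 5–20 noise features, null AUC runs from about 0.51 to 0.68 when validation cases are interpolated toward training neighbours. It runs from about 0.55 to 0.82 when the synthetic validation cases come wholly from the training minority. SMOTE inside the validation fold gives no inflation of AUC over untouched folds.

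**The case against.** The strongest reply is that this is a slip of drafting, not a planned procedure. One predicate has been stretched over a list, and it fits two of the three items. SMOTE has no standard operation to apply to held-out data, so the literal instruction has to be interpreted before it can be coded. The sentence's own aim is separation, and the other two places that discuss imbalance tie it to model training. A reader might infer that the investigators intend to score their models on synthetic patients. The documents do not support that; on balance they point to training-only use. What remains is that the sentence on validation is the most specific rule, names SMOTE, and is not qualified anywhere.

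It is also fair that the damage depends on the metric. The ROC curve, sensitivity and specificity, which the Analysis section names, do not depend on prevalence and move little if SMOTE stays within the validation fold. The measures that do depend on class balance are committed to in the abstract.

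A reader might take a single figure, such as a null AUC of 0.74 (21 distant cases, 20 features, validation cases built wholly from training patients), as the expected bias. It is one cell under one implementation. The article fixes none of those quantities, so only the range can be used.

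A reader might also go on to criticise how clinical variables are filled in for synthetic patients, the claim of generalisable training, or the lack of a preference for class weighting. The handling of mixed variables is implementation detail that an article may leave out. The claim changes no result, and class weighting is already a listed option. None of these belongs in this point.

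**Conclusion.** The point holds as an error of wording in the rule that governs evaluation of the primary outcome. Followed literally, the rule defeats its stated purpose; it does not show what the investigators will in fact do.

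Its size depends on the implementation. Within-fold SMOTE leaves AUC at about 0.50 for noise but moves the precision–recall curve, F-score, accuracy and confusion matrix to an artificial balance, as in the rise of PPV from 0.25–0.43 to 0.75. Synthetic cases that draw on training patients inflate AUC without any signal, from barely (0.51) to severely (0.82) across the conditions examined. These figures rest on an assumed distant share, feature count, fold number and classifier, and the PPV example on an assumed sensitivity and specificity. The direction of the AUC leakage does not hinge on one chosen value, but its amount does.

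The wording should be corrected before the pipeline is coded, because every literal implementation considered distorts at least one listed metric.

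**What to change.** Replace the single rule in the Analysis section with two sentences:

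1. Scaling, feature selection and dimensionality reduction are fitted on the training folds and applied unchanged to the validation folds.
2. SMOTE and any other augmentation are applied to the training folds only, in both the inner and outer loops; all performance metrics are computed on real patients at their observed class ratio.

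This brings the validation rule into line with the training-only wording in Study population and sample size and in the paragraph on class imbalance. The cost is two sentences and a check of where the resampling step sits in the code. The downside is that reported metrics may be lower than under the literal wording.
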